### Study endpoints

The primary endpoint of this study is to determine the effectiveness of a weight reduction diet program based on an innovative and standard product line (meal replacements) through actual reduction of the body mass (BM)/ fat mass (FM) of the participants in relation to their pre-trial body mass (BM)/fat mass (FM).

The secondary study endpoints include:

reduction of waistline and reduction of waist/hip and waist/height ratio;improvement of the participants` lipid profile (increase in HDL/LDL ratio) compared to initial values;improvement of the quality of life of participants;improvement of asthma control, decrease in the number and severity of asthma exacerbations in participants with asthma;decrease in systemic inflammation, decrease in oxidant stress biomarkers.

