### Follow up

Participants will be followed up at regular intervals. Every two months they will undergo a medical physical examination and anthropometric measurements once a month (as discussed in the previous section) and any adverse events recorded on adverse events reporting forms will be discussed. Additionally, their dietary intake and study compliance will be assessed by 3-day food diary and 24-hour dietary recall in each phase of the study. For better adherence to the programme, individual nutritional consultations will be carried out if needed.

After 1, 3, 6, 9 months and at the end of the study, the participants will have blood and urine samples collected. At these timepoints, the participants health status, nutritional status and level of systemic inflammations will be assessed. Stool samples will be taken at baseline and at the end of the study. Design and key timepoints of the study are presented in Fig 1.

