**Fig 2 pone.0306400.g002:**
[figure not shown]
Study phase diagram for active group (innovative and standard). Control group (not shown) has 5 regular low-calory balanced meals throughout the entire course of the study. In each phase. exercise and sufficient fluid intake are required.

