### Statistical analysis

Sample size was calculated as 88: 88: 44 (N = 220 with the test for repeated measures using effect size of D = 0.5 (which represents a medium size clinical effect), SD = 1, power = 0.8 and alpha = 0.05 (minimum group size of 34) using a 15% drop-out rate. Analysis of variance for repeated measurements will be used to determine the effectiveness of individual programs on primary outcomes (BM/FM). The same analysis will be used to analyze secondary performance parameters and safety parameter variables. A chi-square test or Fisher’s test will be used to compare the occurrence of safety-related parameters between groups. The threshold for missing values will be set at 5%. If the missing values for certain variables exceed this threshold, these will be handled by imputing variables according to previously measured or observed values, that is the last observation will be carried forward. The analysis will be done as intention-to-treat (ITT) and as per-protocol (PP). P < 0.05 will be considered statistically significant with appropriate correction for multiple comparisons. The statistical analysis will be performed using STATISTICA 12 program (StatSoft, Tulsa, OK, USA).

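### The repeated-measures ANOVA that decides effectiveness is not tied to a visit or between-arm contrast; over monthly visits its arm-by-time test can be significant when end-of-study losses are equal

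*Protocol article*

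**What the plan says.** All references are to the protocol article.

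- **Study endpoints.** Effectiveness is to be shown "through actual reduction of the body mass (BM)/ fat mass (FM) of the participants in relation to their pre-trial body mass (BM)/fat mass (FM"). No time point is given.
- **Statistical analysis.** The test is named as follows: "Analysis of variance for repeated measurements will be used to determine the effectiveness of individual programs on primary outcomes (BM/FM"). The section does not say which visits enter, whether baseline is one of them, or which term or contrast decides. It promises a correction for multiple comparisons but does not list the comparisons.
- **Follow up.** Participants have "anthropometric measurements once a month", so many more than two values of the primary outcome will exist. Blood and urine follow a sparser schedule: "After 1, 3, 6, 9 months and at the end of the study, the participants will have blood and urine samples collected". The text does not give the month of the final visit.
- **Follow up, Fig 2 legend and Discussion.** The product arms pass through four successive phases after a two-week entry phase. The Discussion describes the first as the most intensive, with the most meal replacements. In contrast, "Control group (not shown) has 5 regular low-calory balanced meals throughout the entire course of the study".
- **Abstract and Introduction.** The programme aims both to reduce weight and to maintain a healthy weight.

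**The concern.** An omnibus interaction over many visits answers a broad question: do the arms differ in change from baseline anywhere along the course? A reader of a weight-reduction and maintenance trial will usually want a narrower answer: by how much do the arms differ in loss at the end?

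The two questions diverge when one arm moves ahead early and the others catch up. This design makes that course plausible, because the product arms are front-loaded and the control regimen does not change. A significant interaction could then be reported as greater effectiveness of the products although no arm had lost more by the end of the study. With three arms, the omnibus F also gives neither the direction of a difference nor the arm responsible.

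**Working it through.** **1. The plan's own figure.** The sample-size text gives "using effect size of D = 0.5 (which represents a medium size clinical effect), SD = 1" and "power = 0.8 and alpha = 0.05 (minimum group size of 34) using a 15% drop-out rate". A two-sided paired t-test reproduces the minimum of 34:

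- Normal approximation: n = ((1.960 + 0.842)/0.5)² = 31.4.
- Solved with the t distribution: n = 33.4, rounded up to 34 (power 0.808).
- A two-sample t-test at d = 0.5 would need 64 per arm.

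So 34 is what a pre-post comparison within one arm requires. This does not prove that such a test was used. A two-sample test on change scores, with SD √(2(1 − ρ)), needs 38 per arm at ρ = 0.70 and 32 at ρ = 0.75 (normal approximation), so a correlation between these could also give 34. Either way, the sample-size text does not show which contrast the ANOVA is meant to deliver.

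**2. What the interaction tests.** Let μ(a,t) be the mean of arm a at visit t, with baseline t = 0. Parallel profiles mean that μ(a,t) − μ(a,0) is the same for all arms at every t. The arm-by-time null is therefore equal change from baseline at every visit jointly. Rejection means unequal change at one or more visits, without saying which.

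**3. Two time points.** With only baseline and end entered, the interaction is the one-way ANOVA on change. In one simulated data set both gave F = 2.287 and p = 0.1045.

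**4. Equal final loss with a temporary lead, in kg.** From the document: three arms, and "Sample size was calculated as 88: 88: 44 (N = 220 with the test for repeated measures", less 15% drop-out (88 × 0.85 = 74.8, taken as 75; 44 × 0.85 = 37.4, taken as 37). Assumed, because the document gives no values: 12 months of monthly visits, baseline SD 15 kg, SD of 12-month change 6 kg, visit noise 1 kg, and random-slope or random-walk covariance. Both product arms lead control by the stated amount at month 3, and the lead shrinks to zero by month 12.

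| Lead at month 3 | Arm-by-time F, Greenhouse-Geisser corrected | One-way F on final change |
|---|---|---|
| 1 kg | about 8-10% | about 5% |
| 2 kg | about 30-33% | about 5% |
| 3 kg | about 76-97% | about 5% |

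Entries are the percentages of simulated trials with p < 0.05. The ranges reflect the assumed covariance.

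**5. The same question in SD units, under other assumptions.** Here the arms are 88:88:44, with visits at 0, 1, 3, 6, 9 and 12 months and 2,000 trials per setting. The correlation is a constant 0.8, or autoregressive at 0.97 per month.

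| Peak lead | Arm-by-time F, ρ = 0.8 | Arm-by-time F, autoregressive | Final change |
|---|---|---|---|
| 0.15 SD | 23% | 14% | 4-6% |
| 0.25 SD | 62% | 47% | 4-6% |
| 0.35 SD | 93% | 91% | 4-6% |
| 0.50 SD | 100% | 100% | 4-6% |

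With 75:75:37 completers the interaction rejects in 13-100%.

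**6. Power if the arms really diverge.** With steady divergence to 0.5 SD at the end (ρ = 0.8, 88:88:44), the corrected interaction has 99% power and the final-change test 98.5%. A named end-of-study contrast makes the answer clearer; it does not bring a consistent gain in power.

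**The case against.** The strongest reply has four parts.

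- **The ANOVA does address reduction.** A reader might infer that the named test does not test reduction from pre-trial mass at all. The document does not support that: with baseline as a time point, the interaction null is equal reduction at every visit (step 2). This part of the reply stands.
- **The endpoint has no date.** A reader might take the rejection rates above as type I error rates of the plan. They are not. In the simulations the product arms truly lose more at early visits, so rejection is a correct answer to whether reduction ever differs. It misleads only if the question is end-of-study loss. That reading fits the aim of reducing and maintaining weight, but the endpoint does not state it.
- **The article does not say that all visits enter.** Monthly measurement is a data-collection schedule, and with two time points the problem vanishes. This stands, and the point is conditional on it. A reader might also criticise the arm main effect averaged over visits, but nothing in the article says that this term decides.
- **The detail may be elsewhere.** The article refers to a fuller protocol in supplementary material, and an analysis plan may exist. The absence of detail is therefore not the fault raised. What remains is that the article does fix an omnibus method as the effectiveness test, in a design where such a test and end-of-study loss can disagree.

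**Conclusion.** The point holds in a limited, conditional form. The named analysis is compatible with the endpoint but does not isolate the reduction at any chosen visit. If the monthly visits enter, a significant arm-by-time F would not by itself show that end-of-study losses differ.

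The size depends on the temporary lead: small at 1 kg, material at 2 kg and dominant at 3 kg. These figures rest on an assumed 12-month course, assumed SDs and a lead that disappears completely, none of which is in the document. If only baseline and end of study enter, there is no problem.

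This should be put right before analysis. It is not evidence that the planned test is invalid.

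**What to change.** In the Statistical analysis section, name the between-arm difference in change in BM/FM from baseline to the end-of-study visit as the confirmatory contrast. Estimate it as a visit-specific contrast from a longitudinal model, or by ANCOVA at that visit adjusting for baseline. Keep the monthly profile and the arm-by-time F as supportive, to describe when the arms separate or converge. State the same time point in Study endpoints so that endpoint and test agree.

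The cost is wording only, since the monthly and end-of-study measurements are already planned. The downside is that a difference confined to the intensive phase would no longer count as primary success. If the sponsor wants such a difference to count, the endpoint should say so and name its own visit.

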The study protocol is defined in detail in Supplementary material. This study will encompass 4 phases of different duration and design for adults and pediatric participants): initial phase (intensive), active phase, stable phase and monitoring phase, preceded by an entry phase of adaptation to the study protocol (duration of entry phase: 2 weeks). The study phase diagram is shown in Fig 2.

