All study results and newly acquired knowledge will lead to the development of multidisciplinary nutritional support in the form of a counseling center that will help improve nutritional and other guidelines that will be individually tailored according to specific needs of each patient and disease subtype. One of the possible limitations of our study may be a significant drop-out rate. As the study protocol is intense at certain phases, a certain proportion of the participants may lose interest in participating in the study and not show up for regular check-up visits. This will be mitigated by recruiting a larger number of participants in the clinical study in both child and adult groups at baseline to account for drop-outs. Another way of minimizing the drop-out rate will involve continuous psychological support provided by experts in the field of eating behaviors and cognitive behavioral therapy. additionally, since the first phase of the study is the most intensive one (stringent dietary intake) and has the most meal replacement products (MRP) included, it will be the hardest phase to pass. Therefore, the MRPs will be designed to be of appealing taste and texture.

An additional bias might be over representation of the female gender in each of the populations, as asthma after puberty is more common in women (girls) than in men (boys).

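### Carry-forward above a 5% missing-data trigger will almost certainly govern the primary BM/FM analysis and biases it by an amount and in a direction that the plan cannot fix

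*Protocol article*

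**What the plan says.** All of the rule stands in the protocol article, section Statistical analysis:

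- BM/FM, the primary outcome, is analysed by repeated-measures analysis of variance, in both an ITT and a per-protocol set.
- A 5% limit on missing values is set, and "If the missing values for certain variables exceed this threshold, these will be handled by imputing variables" from earlier measurements; "that is the last observation will be carried forward".
- The sample size was obtained "using a 15% drop-out rate".
- The rule has no exception for BM/FM and is not confined to one analysis set.

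Other sections bear on it. Study endpoints defines the primary endpoint as change from the pre-trial value. Follow up schedules anthropometry monthly and describes an "initial phase (intensive), active phase, stable phase and monitoring phase". The Fig 2 caption gives one phase diagram for both meal-replacement groups and says that control keeps five low-calorie meals throughout. The Discussion concedes that "One of the possible limitations of our study may be a significant drop-out rate" and says of the first, intensive phase that "it will be the hardest phase to pass".

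**The concern.** Planned drop-out is three times the trigger, so carry-forward is in effect the planned handling of the primary outcome. It replaces a drop-out's unknown end-of-study weight with the last recorded one. That is right only if weight does not change after the participant leaves. A programme built in phases of different intensity is designed on the expectation that weight will move.

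The carried value depends on when the participant left and on the regimen followed until then. The regimen is phased in the two active arms and constant in control, so the error in the active arms need not equal the error in control. The endpoint is also a change within each arm, and there nothing offsets the error. In addition, the analysis treats each imputed value as a measurement, so standard errors understate the uncertainty. At stake are the size of the primary effect and the error rate of its test.

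**Working it through.** **Inputs from Statistical analysis:** trigger 5%; planned drop-out 15%; N = 220 (88:88:44); effect size 0.5 with SD 1; minimum group size 34. **From Study population:** recruitment target 240. **Assumed, because the documents give none:** weight trajectories, time of drop-out, drop-out by arm.

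**1. The plan's own figure.** A within-group (paired) t-test with effect 0.5, two-sided alpha 0.05 and power 0.80 needs 33.4 participants, rounded up to 34, as stated. So 0.5 SD is the planned effect and serves as the yardstick in step 4. With 15% loss, 34 / 0.85 = 40, whereas the smallest group is 44, which would allow 1 - 34/44 = 22.7% loss. That mismatch is a separate matter. A loss above 15% would only move the study further past the trigger.

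**2. Will the trigger be met?**

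- N = 220: expected missing at the end 0.15 x 220 = 33; trigger 0.05 x 220 = 11.
- N = 240: 0.15 x 240 = 36; trigger 0.05 x 240 = 12.
- If true loss is 15%, the binomial probability of more than 5% missing is 0.9999976 (N = 220) or 0.9999992 (N = 240).

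The text does not say whether the 5% is counted per visit or over all visits of a variable. Counted over all visits, 15% drop-out exceeds 5% once drop-outs miss on average more than 0.05 / 0.15 = one third of the visits. Early leavers would do so.

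**3. Bias in kg.** Bias in an arm mean = drop-out proportion x (carried value - true end value). The bias in the difference is active minus control. All weights are assumed changes from baseline.

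| Case | Active: carried, end, drop-out | Control: carried, end, drop-out | Active bias | Control bias | Bias in difference |
|---|---|---|---|---|---|
| A: leave after early loss, later regain | -8, -5, 15% | -2, -4, 15% | 0.15 x (-3) = -0.45 | 0.15 x 2 = +0.30 | -0.75 kg |
| B: as A, more drop-out in active | -10, -6, 25% | -2, -4, 10% | 0.25 x (-4) = -1.00 | 0.10 x 2 = +0.20 | -1.20 kg |
| C: leave before most of the loss | -2, -8, 15% | -1, -4, 15% | 0.15 x 6 = +0.90 | 0.15 x 3 = +0.45 | +0.45 kg |

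In case A a true difference of -1.0 kg is estimated as -1.75 kg. In case C a true difference of -4.0 kg is estimated as -3.55 kg. Drop-out is equal in both arms in A and in C, so equal drop-out does not remove the bias.

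**4. Bias in SD units.** At 15% drop-out, with a gap between carried and true end value of 0.25, 0.5 or 1.0 SD, an arm mean shifts by 0.15 x gap = 0.0375, 0.075 or 0.15 SD. That is 7.5%, 15% or 30% of the planned effect of 0.5.

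**5. Type I error.** Simulation with equal true end means, 88 v 44, SD 1, correlation 0.8 between carried and end value (assumed), two-sample t-test at the end of the study, 10,000 runs, nominal level 0.05:

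| Drop-out active/control | Active carried value too low by | Type I error |
|---|---|---|
| 15% / 15% | 0 | 0.052 |
| 15% / 15% | 0.5 SD | 0.066 |
| 15% / 15% | 1.0 SD | 0.117 |
| 20% / 5% | 0.5 SD | 0.082 |
| 30% / 10% | 0.5 SD | 0.117 |

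The t-test stands in for the planned repeated-measures analysis, so these values show scale only. Because the test is two-sided, a carried value too high by the same amount gives the same rates.

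**The case against.** The best reply is that the documents do not establish which way the result is bent. Two stronger readings are tempting, and neither is supported.

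**That carry-forward favours the meal-replacement arms.** This needs regain after drop-out, or more drop-out in those arms. The article names the phases but gives no weight trajectory, no regain and no drop-out by arm. Its own remark that the first phase is the hardest suggests that people may leave during it, near baseline weight. Carry-forward would then understate the loss, as in case C. The direction must stay open.

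**That nothing is done at or below 5%, so incomplete rows are deleted and the ITT set shrinks.** The text is silent there; it states no such decision. A figure for the loss would need a number of visits that the article does not give and a pattern of missingness that is unknown. Such detail may stand in the full protocol or analysis plan, which are not shown. The absence of a missing-data sensitivity analysis is no finding for the same reason.

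Two further limits stand. The innovative and standard groups share one phase diagram, so with similar drop-out and similar trajectories their errors would largely cancel. The per-protocol set may hold few carried values, although its definition is not given. With equal 15% drop-out and a 0.5 SD gap, the inflation of type I error is also modest (0.066).

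None of this defends the rule itself. It is stated, its trigger sits at a third of the planned loss, and a primary estimate with bias of unknown sign is not protected by that ignorance.

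**Conclusion.** The point holds as a badly chosen, explicitly stated rule for the primary outcome. If drop-out is near the planned 15%, carry-forward will apply to end-of-study BM/FM, and the ITT result is the one mainly exposed. Within-arm change and the active-versus-control contrasts can be biased even when drop-out is equal, and uncertainty is understated.

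The size rests on assumed trajectories: -1.2 to +0.45 kg in the three cases shown, or 7.5% to 30% of the planned effect in a single arm mean for gaps of 0.25 to 1.0 SD. These are illustrations, not predictions. The conclusion does not depend on any one of them. It needs only that weight changes after drop-out, which the phased design leads one to expect.

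**What to change.** - Remove the 5% trigger and carry-forward from the primary analysis.
- Analyse all observed monthly BM/FM values from every randomised participant, at any level of missingness, with a likelihood-based mixed model for repeated measures containing arm, visit and their interaction. Multiple imputation would also serve. Both normally rest on data missing at random, and the plan should say so.
- Keep carry-forward at most as a sensitivity analysis. Preferably add one analysis that allows data to be missing not at random, for instance with drop-outs assumed to follow control or to move back toward baseline weight.
- Make the change before unblinding.

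The cost is revised analysis wording, a little more analysis work, and different software if the named package cannot fit the model. The monthly measurements are already planned, so no visit or sample-size change is needed.

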## Results

The data that will be collected in this study is shown in Table 1.

At the end of the study, the results of diagnostic tests, anthropometric and other measurements will be analyzed and compared with clinical, molecular (genetic and epigenetic) data and other data collected during the study (such as data on physical activity). Additionally, all results will be integrated into an innovative (bio)informatics platform. In consultation with experts in medical, molecular-genetic, bioinformatics, and food-biotechnological specialties, the clinical significance of the obtained results and their importance for each individual patient will be defined and a personalized programme for body weight reduction will be designed.

## Discussion

Despite numerous studies on individual subtypes of asthma, knowledge about the causative agents and etiological factors of the disease is still insufficient. Generalized guidelines are used, which do not provide full insight into the specific biological processes of asthma. The financial costs of asthma treatment are significant and include direct medical (diagnosis, medications, hospitalization) and indirect costs, including reduced quality of life for both the patients and their families (especially in children with asthma) and reduced work ability. The concept of precision medicine implies that different asthma phenotypes and endotypes need to be identified in order to optimize and improve treatment [12]. With effective prevention programmes and therapeutic measures based on a personalized approach, it is possible to avoid most of these costs.

Obesity is a significant social problem that has expanded to a global scale over the last few decades. Additionally, obesity is a common comorbidity in asthma and an independent risk factor for asthma development [13].

Asthma symptoms in obese patients are more significant and frequently lead to acute exacerbation and impaired quality of life. Research conducted on 1,000 people showed that symptoms in obese asthmatics led to hospitalization five times more often than within the healthy weight asthmatics [14]. Moreover, obesity in asthma represents a special phenotype of the disease called “obese asthma”, with complex relationships between metabolic and immune dysregulation (pro-inflammatory) [15].

Despite the fact that the clinical manifestations of this phenotype are well described, the etiological and pathophysiological mechanisms underlying obese asthma remains elusive. This study will aim at identifying new pathophysiological mechanisms involved in the development of the disease and enable better monitoring of the progress, degree of asthma control and risk for exacerbations asthma, and treatment success. The purpose of this study is design and develop an improved and personalized management approach that focuses directly on the causes of the diseases and not just the symptoms. Weight loss in obese individuals with diagnosed asthma is associated with symptom improvement and reduction of medication use [16]. Evidence shows that structured, personalized body weight reduction programs that include nutritional interventions (such as meal replacements and the introduction of a balanced diet) and lifestyle changes (including physical activity) may have a significant effect on improving the health status of the subjects as well as reducing the risk of cardiovascular diseases and metabolic syndrome [17].

The outcomes of this study may significantly contribute to the improvement of health care utilization, reducing the financial burden for the cost of treatment due to the decrease in the number of chronic patients with pronounced symptoms and the number of cases requiring hospitalization and ultimately improve the quality of life of vulnerable groups (children, patients). Furthermore, the results of this study will provide better insight into the regulatory mechanisms driving inflammation in obesity and asthma and may will serve as a basis for further research on the same or related topic, as well as research into environmental and intrinsic factors with the development of asthma in children and their association with global and gene-specific epigenetic variations.

All study results and newly acquired knowledge will lead to the development of multidisciplinary nutritional support in the form of a counseling center that will help improve nutritional and other guidelines that will be individually tailored according to specific needs of each patient and disease subtype. One of the possible limitations of our study may be a significant drop-out rate. As the study protocol is intense at certain phases, a certain proportion of the participants may lose interest in participating in the study and not show up for regular check-up visits. This will be mitigated by recruiting a larger number of participants in the clinical study in both child and adult groups at baseline to account for drop-outs. Another way of minimizing the drop-out rate will involve continuous psychological support provided by experts in the field of eating behaviors and cognitive behavioral therapy. additionally, since the first phase of the study is the most intensive one (stringent dietary intake) and has the most meal replacement products (MRP) included, it will be the hardest phase to pass. Therefore, the MRPs will be designed to be of appealing taste and texture.

An additional bias might be over representation of the female gender in each of the populations, as asthma after puberty is more common in women (girls) than in men (boys).

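### Over-recruitment protects precision only: if drop-out is heavier in the meal-replacement arms and related to outcome, the comparison with control can be biased at any sample size, and LOCF does not repair it

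*Protocol article*

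**What the plan says.** The Discussion introduces the limitation: "One of the possible limitations of our study may be a significant drop-out rate". The reason given is general and names no arm: "As the study protocol is intense at certain phases, a certain proportion of the participants may lose interest in participating in the study". Three measures follow.

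- Recruitment: "This will be mitigated by recruiting a larger number of participants in the clinical study", for children and adults alike, to allow for those lost.
- Support: "Another way of minimizing the drop-out rate will involve continuous psychological support provided by experts".
- Palatability. The first phase is described as the most intensive, with stringent intake and the largest share of meal replacements, and "it will be the hardest phase to pass". The response is: "Therefore, the MRPs will be designed to be of appealing taste and texture".

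The Fig 2 phase diagram covers the innovative and standard groups only. Its legend adds: "Control group (not shown) has 5 regular low-calory balanced meals throughout the entire course of the study".

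Statistical analysis uses one drop-out rate of 15% for all arms, a minimum group size of 34, and 88:88:44 (N = 220). Study population sets recruitment at 240. Body mass and fat mass are the primary outcomes, analysed by repeated-measures ANOVA on both an intention-to-treat (ITT) and a per-protocol basis. Where more than 5% of a variable is missing, the last observation is carried forward. Follow up schedules anthropometric measurements monthly.

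**The concern.** Drop-out threatens a randomised comparison in two ways. It reduces numbers, and it can leave groups that are no longer comparable. Over-recruitment addresses only the first.

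The second is a real possibility here because the feature that the Discussion singles out as hardest is absent from the control arm. Suppose those who do poorly on the products stop attending and their later weight is never taken. The product arms are then judged partly on a selected group or on carried-forward early weights, while control stays closer to complete. A larger trial then estimates the wrong quantity more precisely. At stake is the product-versus-control contrast on the primary outcome. The innovative-versus-standard contrast is less exposed, because both arms share the phase structure and may lose participants at similar rates.

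**Working it through.** **1. The plan's own head-count.** A paired t-test with d = 0.5, two-sided alpha 0.05 (sidedness assumed) and power 0.8 needs n = 34 (power 0.808), which matches the stated minimum. Inflating for 15% gives 34 / 0.85 = 40, against the plan's 44 in the smallest arm; that mismatch is a separate matter. An arm of 44 can lose 10 / 44 = 22.7% and keep 34. With 240 recruited, the smallest arm is 48 and can lose 14 / 48 = 29.2%. On the plan's own within-group basis, numbers are therefore covered. Comparability is what remains exposed.

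**2. Does a larger N remove the bias?** Assumptions: 15% overall drop-out at 2:2:1; outcome in SD units; correlation ρ between drop-out propensity and poor outcome. If a fraction d of an arm drops out, the mean among those remaining shifts by ρ × φ(z) / (1 − d), where z is the normal quantile at 1 − d. N does not appear in this expression.

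- All loss in the product arms (0.8 × 18.75% = 15%), ρ = 0.5: z = 0.887, φ(z) = 0.269, shift = 0.5 × 0.269 / 0.8125 = 0.17 SD.
- 17% versus 7% (0.8 × 17% + 0.2 × 7% = 15%), ρ = 0.5: 0.152 − 0.072 = 0.08 SD.
- ρ = 0: shift = 0, however unequal the loss.

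Simulation of one product arm against control, completers only, agrees:

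| Drop-out, product vs control | ρ | Bias (SE) at 88 vs 44 | at 4× | at 16× |
|---|---|---|---|---|
| 18.75% vs 0% | 0.5 | 0.167 (0.193) | 0.174 (0.092) | 0.167 (0.048) |
| 17% vs 7% | 0.5 | 0.085 (0.183) | 0.080 (0.094) | 0.079 (0.046) |
| 18.75% vs 0% | 0 | −0.006 (0.197) | 0.003 (0.096) | −0.002 (0.046) |
| 15% vs 15% | 0.5 | −0.006 (0.190) | −0.004 (0.095) | 0.003 (0.047) |

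Bias needs both unequal loss and a link to outcome. Where both hold, it does not shrink as the trial grows.

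**3. LOCF when leavers regain.** Assumptions: drop-out 17.5% (products) and 5% (control), so 0.8 × 17.5% + 0.2 × 5% = 15%; stayers lose 1.0 SD and 0.5 SD; leavers end with no loss. Let f be the share of the stayers' loss that leavers had reached at their last visit, the same in both arms.

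- True difference: 0.825 × 1.0 − 0.95 × 0.5 = 0.825 − 0.475 = 0.35 SD.
- LOCF: (0.825 + 0.175f) − (0.475 + 0.025f) = 0.35 + 0.15f. At f = 0 this is 0.35 (no bias), at f = 0.2 it is 0.38 (+9%), and at f = 0.5 it is 0.425 (+21%).
- Completers: 1.0 − 0.5 = 0.50 SD, and 0.50 / 0.35 = 1.43 (+43%).

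**4. LOCF when leavers would have kept losing.** Assumptions: 18.75% versus 0% drop-out; mean final losses 1.5 SD and 1.0 SD had all been measured (true difference 0.5 SD). The bias is −0.1875 × 1.5 × (1 − f), which is −0.225 at f = 0.2, −0.141 at f = 0.5 and −0.056 at f = 0.8. The sign is reversed.

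**The case against.** The strongest reply has four parts.

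- **The arm split is inferred.** The Discussion speaks of participants in general and hedges throughout. Stringent intake is also given as a reason why the first phase is hard, control participants are on a reduced-calorie diet too, and every arm has an exercise programme. This stands: heavier loss in the product arms is likely from the Discussion and Fig 2 legend together, but it is not stated.
- **Over-recruitment is not the only measure.** Psychological support and palatability aim to reduce drop-out itself, the second specifically in the product arms. The extra recruitment is described as allowing for losses, not as restoring comparability. This also stands, but neither measure obtains a weight from someone who still leaves.
- **The plan has an ITT analysis with LOCF.** At 15% loss the 5% threshold is passed, so the completers' figure of 43% is not the plan's ITT result. This stands. LOCF nevertheless gives the right answer only in special cases, such as f = 0 in step 3.
- **Follow-up after stopping may be covered in the supplementary protocol, which is not shown.** This is fair, so its absence from the article is not the finding. The finding rests on what the article does fix: over-recruitment offered as mitigation, and LOCF as the named missing-data method.

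A reader might also infer that the plan equates stopping the diet with leaving the study. The Discussion describes only people who cease to attend, and nothing in the article says that stopping the products ends follow-up.

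**Conclusion.** The point holds in a conditional form. Over-recruitment protects precision only. If loss is heavier in the product arms, as the design makes likely, and related to outcome, the product-versus-control comparison can be biased at any sample size. LOCF does not correct this.

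No single size or direction can be claimed, because the document gives no drop-out by arm and no link to outcome; all such inputs above are assumptions. Under them, LOCF ranges from 21% too high (leavers regain, f = 0.5) to 0.225 SD too low (leavers would have kept losing, f = 0.2). A completers' comparison, which a per-protocol analysis may resemble, ranges from about no bias to 43% too high.

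A reader might conclude that the trial will overstate the product effect by 43%. The document does not support that: the figure ignores LOCF and depends on the assumed regain. This is a cheap improvement worth making before outcome data are lost, not a flaw that invalidates the design.

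**What to change.** - **Follow up:** state that participants who stop the assigned products or diet are still asked to the scheduled anthropometric visits. At minimum, seek an end-of-study weight and body-composition measurement from every randomised participant who has not refused. This concerns measurement only and changes nothing about who stops treatment or why.
- **Statistical analysis:** use these observed values in the ITT analysis in place of carried-forward ones, and report drop-out by arm and phase.
- **Discussion:** reword the sentence on recruitment to say that it protects precision only.

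If the supplementary protocol already provides for such follow-up, the article need only say so and align the analysis wording. The cost is some extra contact effort at visits already scheduled, with no new procedure. The ITT estimate may turn out less favourable to the products. Weights not taken at the time cannot be recovered later.
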